# A randomised controlled trial of energetic activity for depression in young people (READY): a multi-site feasibility trial protocol

**DOI:** 10.1186/s40814-020-00734-7

**Published:** 2021-01-04

**Keywords:** Depression, Low mood, Young people, Exercise, Physical activity, Behaviour change, Feasibility trial

## Abstract

**Background:**

Prevalence of depression is increasing in young people, and there is a need to develop and evaluate behavioural interventions which may provide benefits equal to or greater than talking therapies or pharmacological alternatives. Exercise could be beneficial for young people living with depression, but robust, large-scale trials of effectiveness and the impact of exercise intensity are lacking. This study aims to test whether a randomised controlled trial (RCT) of an intervention targeting young people living with depression is feasible by determining whether it is possible to recruit and retain young people, develop and deliver the intervention as planned, and evaluate training and delivery.

**Methods:**

The design is a three-arm cluster randomised controlled feasibility trial with embedded process evaluation. Participants will be help-seeking young people, aged 13–17 years experiencing mild to moderate low mood or depression, referred from three counties in England. The intervention will be delivered by registered exercise professionals, supported by mental health support workers, twice a week for 12 weeks. The three arms will be high-intensity exercise, low-intensity exercise, and a social activity control. All arms will receive a ‘healthy living’ behaviour change session prior to each exercise session and the two exercise groups are energy matched. The outcomes are referral, recruitment, and retention rates; attendance at exercise sessions; adherence to and ability to reach intensity during exercise sessions; proportions of missing data; adverse events, all measured at baseline, 3, and 6 months; resource use; and reach and representativeness.

**Discussion:**

UK National Health Service (NHS) policy is to provide young people with advice about using exercise to help depression but there is no evidence-based exercise intervention to either complement or as an alternative to medication or talking therapies. UK National Institute for Health and Care Excellence (NICE) guidelines suggest that exercise can be an effective treatment, but the evidence base is relatively weak. This feasibility trial will provide evidence about whether it is feasible to recruit and retain young people to a full RCT to assess the effectiveness and cost-effectiveness of an exercise intervention for depression.

**Trial registration:**

ISRCTN, ISRCTN66452702. Registered 9 April 2020.

## Introduction

### Background and rationale

The prevalence of depression amongst young people is high worldwide and recorded rates have increased significantly since the 1980s [1–3]. Depression levels rise sharply as children transition into adolescence, with estimates of depression reported to be between 4 and 11% in mid-to-late adolescence (15–16 years old) and up to 20% by late adolescence (up to 18 years old) [3–5], although prevalence estimates vary widely across studies and countries [4]. A noted trend is the rise in prevalence of depression amongst adolescent females compared to males, estimated at 2:1 [1–4, 6–10]. By 13–15 years, more girls are diagnosed with depression compared to boys [11]. The reasons for this trend are not fully understood but may be related to hormonal changes during puberty, or the tendency for greater internalisation of emotion in girls [4]. These findings are supported by a recent large-scale survey in England (aged 11–15) which found poorer emotional health and wellbeing amongst adolescent girls compared to boys [12, 13]. Evidence also suggests that there are significant disparities in mental health experiences amongst specific groups of young people. For example, those identifying as lesbian, gay, bisexual, and transgender (LGBT) report experiencing depression and anxiety, suicidality, and self-harm at considerably higher rates than heterosexual young people of a similar age, influenced by factors such as bullying and perceived stigma [14, 15]. Available research also points to higher rates of symptoms amongst youth from Black and Asian minority ethnic (BAME) backgrounds [16, 17]. This reflects a complex interplay of the clustering of multiple disadvantages, and the concept of double minorities highlights how factors such as race/ ethnicity and gender identity can further compound mental well-being [18].

Recent research suggests that young people who seek help benefit from contact with mental health services. The UK-based ROOTS longitudinal cohort study found that contact with mental health services by 14-year-olds with depression reduced the likelihood of depression by age 17 [7]. This is particularly important as it is known that many young people with depression do not access mental health services, estimated at 34–56% internationally [7], or delay seeking help, increasing the duration or risk of recurrent episodes [7]. There are, however, concerns regarding the use of antidepressant drugs for those younger than 18 years. Recent meta-analyses suggest that antidepressants for children and adolescents do not generally perform better than placebos [19] and pose an increased risk for suicidal thoughts and aggressive behaviour [20]. For this reason, it is important to identify a range of effective non-pharmacological alternatives to increase the available options for treatment.

One such alternative is psychological approaches that include cognitive behavioural therapy (CBT) and interpersonal psychotherapy. CBT has been shown to be effective in lowering risk of depression in children and adolescents living with subclinical depression [21]. Interpersonal psychotherapy is also beneficial for adolescents living with depression, but few trials compare efficacy with alternative treatments [22]. When treatment outcomes were compared across different therapy types, there was no evidence that one was superior and only 8–27% of the 11–17-year-old participants completed the recommended number of sessions [23]. These findings are echoed by the latest national data suggesting that only 36% of people complete the full Improving Access to Psychological Therapies treatment [24]. Given the cost of delivering individual face-to-face psychological therapies and the low completion rates, there is a need for alternative approaches which promote changes in health behaviours such as exercise. Promoting aerobic exercise can also provide additional improvements in cholesterol and blood lipids, blood pressure, metabolic syndrome, overweight and obesity, and bone mineral density [25], and health-related quality of life [26].

There is clear evidence for the effectiveness of exercise to support adults living with depression, with a recent meta-analysis of exercise finding large significant effects on depression [27]. However, for young people living with depression, the evidence base is scarce and evidence quality is poor. A Cochrane review in 2006 [28] and subsequent systematic reviews in 2013, 2016, and 2018 [29–31] examined the effects of exercise interventions in reducing depression and anxiety in children and adolescents. Larun et.al [28]. and Brown et.al [29]. found a small effect in favour of exercise interventions compared to control groups. Carter and colleagues [30] found a moderate effect on depressive symptoms in clinical samples. Bailey et.al [31]. also reported that exercise was an acceptable and feasible intervention for this target group, with low dropout. However, the low quality of the studies, the small number of studies, small sample sizes, and diversity of participants, interventions, and methods of measurement limit the ability to draw firm conclusions. There is a need for well-powered and robust trials with help-seeking young people in real-world treatment settings that explore effectiveness alongside the mechanisms by which exercise help and what impact intensity of exercise has on depression.

There are several mechanisms that have been proposed to explain the many ways by which exercise may be beneficial in the management of depression [32]. Some of these might be via social mechanisms; exercise participation can provide a diversion from depressive thoughts, opportunities to learn new skills, and increased socialisation [33]. In addition, there may be physiological mechanisms; exercise is associated with promoting the release of endorphins and serotonin which can improve mood [34]. Further, inflammation has been identified as a potential contributor to the development of depression [35], suggesting that anti-inflammatory strategies, such as regular exercise [36], may be effective at preventing and managing depressive symptoms.

The optimal intensity of exercise required has not been established, and this information is critical when determining exercise on prescription for depression. Moderate levels of exercise have been shown to increase myokines (proteins released by muscle cells) which could have a positive impact on inflammation [37] and hence depression. In recent years, it has come to light that performing very short bursts of high-intensity exercise (30 s) followed by 30 s of rest repeated for 4 min has produced increased fat oxidation and increased maximal oxygen uptake [38]. Furthermore, research has suggested that high-intensity interval training (HIIT) can promote anti-inflammatory effects during recovery [39] and therefore could be beneficial for diseases with an inflammatory response [40, 41]. There remains considerable uncertainty about the extent to which exercise intensity is related to benefit for depression.

Overall, young people are underserved by child and adolescent mental health services and at high risk of continued mental health problems into adulthood. There is an urgent need to offer feasible, acceptable, and cost-effective treatment options for this group, given the limitations and potential risks of pharmacotherapy treatment and long waiting times for psychological support. NICE clinical guidance [42] recommends that adolescents with depression should be offered advice on the benefits of regular exercise and encouraged to follow a structured and supervised exercise programme of up to three sessions a week, 45–60 min, for 10–12 weeks. Consequently, current NHS policy and practice regarding exercise is to provide guidance rather than a structured and supervised exercise intervention. However, the NICE guidance is based on weak evidence (level IV) due to a lack of high-quality studies in this area. The current study will ascertain the feasibility of conducting a large, adequately powered, high-quality RCT with help-seeking young people with depression. Additionally, given pressure on NHS budgets and the many competing uses of NHS resources, it is not sufficient to show that an intervention is effective, we must also show it represents good value for money compared to other potential uses of these resources, i.e., that it is cost-effective. Our research will also add important knowledge regarding the feasibility of partnership working across the NHS and local community organisations, such as Active Partnerships, in areas with diverse populations and deprivation, to improve mental health support for young people [9, 43].

In summary, the existing evidence suggests that exercise may be a promising and acceptable intervention for young people living with depression. There is clear need to test the feasibility of running a high-quality trial in this area, in terms of recruitment and retention of young people, development, training, and delivery of the intervention as planned, and provide data to inform a full trial.

### Objectives

The objective is to establish the feasibility of conducting a full RCT with embedded process evaluation and parallel cost-effectiveness, with user and stakeholder input in multiple English counties (Hertfordshire, Bedfordshire, Norfolk). It will determine whether it is possible to recruit and retain young people to the trial, develop and deliver the intervention as planned, evaluate the training and delivery of the intervention, and will provide data to inform the design of the main trial (e.g. required sites and sample size).

### Trial design

A three-arm, multi-site, 12-week cluster randomised controlled feasibility trial with 6-month follow-up.

## Methods

### Participants, interventions, and outcomes

#### Study setting

The READY feasibility trial is taking place in Hertfordshire, Bedfordshire, and Norfolk with GP involvement. The intervention will be delivered by registered exercise professionals (REP), employed by local physical activity providers (e.g. Watford FC Community and Sports Trust, Active Luton, Norwich City FC Community Sports Foundation), in local community venues (e.g. sports facilities and community halls).

#### Eligibility criteria

The inclusion criteria includes help-seeking young people aged 13–17 years with a Children’s Depression Inventory (CDI 2[44]) score between 17 and 36 (mild to moderate symptoms), who understand their role in the trial and are able to complete trial activities, who can get to the intervention venue, consent to participate, with the consent form being completed for parent/carer for under 16 s and consent of parent/carer to provide data and take part in the study, and both young person and parent/carer able to complete the questionnaires in English. Current treatment with antidepressants or other drug(s) or psychological therapy is allowed.

The exclusion criteria includes being considered unsuitable by the clinician screening for eligibility, their current treatment or co-morbid conditions presenting contraindications to engaging in the RCT or exercise, active psychosis, significant substance abuse, self-harm, or suicidal ideation presenting significant risk (assessed as part of the Development and Wellbeing Assessment (DAWBA)).

#### Interventions

The intervention sessions will run twice a week for 12 weeks, with a 15–20 min ‘healthy living’ behaviour change portion of the session (in all arms), followed by the exercise or social portion of the sessions. The proposed exercises are based on research by Weston et al. [45] who developed an exercise protocol from qualitative data collected at focus groups from adolescent school children. It incorporates activities which will appeal to both males and females and has been designed with the consultation of a range of young people.

##### High-intensity exercise arm

This is composed of high-intensity exercises of alternating training sessions [45, 46] (e.g. basketball, football, boxing drills—see Table 1 for full breakdown) beginning with a 10-min warm up, culminating with a 5-min whole body cool down. Young people will perform four repetitions of 45 s of maximal effort exercise (> 90% predicted maximal heart rate) with 90 s rest in between each repetition (approximately 9 min). This will increase by 2 min and 15 s every 2 weeks (e.g. one repetition of 45 s of exercise and 90 s rest) for the first 6 weeks and 4 min 30 s (e.g. two repetitions of 45 s of exercise and 90 s rest) in the last 6 weeks. The final 2 weeks will be 12 repetitions (27 min of exercise). Heart rate monitors will be used to tailor each person’s maximum intensity and measure exertion in each session [47].

**Table 1 Tab1:** Exercise session outline

Week	Session number	High-intensity exercise component	Low-intensity exercise component
1	1	10 min warm up Boxing (4 reps of 45 s and 90 s rest) 5 min cool down **Total time: 24 min**	10 min warm up Walking football (7.5 min halves) *2 min rest at half time* 5 min cool down **Total time: 32 min**
	2	10 min warm up Circuit training to music (4 reps of 45 s and 90 s rest) 5 min cool down **Total time: 24 min**	10 min warm up Walking netball (7.5 min halves) *2 min rest at half time* 5 min cool down **Total time: 32 min**
2	3	10 min warm up Football (4 reps of 45 s and 90 s rest) 5 min cool down **Total time: 24 min**	10 min warm up Walking basketball (7.5 min halves) *2 min rest at half time* 5 min cool down **Total time: 32 min**
	4	10 min warm up Basketball (4 reps of 45 s and 90 s rest) 5 min cool down **Total time: 24 min**	10 min warm up Walking dodgeball (7.5 min halves) *2 min rest at half time* 5 min cool down **Total time: 32 min**
3	5	10 min warm up Choice/combination (5 reps of 45 s and 90 s rest) 5 min cool down **Total time: 26 min 15 s**	10 min warm up Walking choice (9 min halves) *2 min rest at half time* 5 min cool down **Total time: 35 min**
	6	10 min warm up Boxing (5 reps of 45 s and 90 s rest) 5 min cool down **Total time: 26 min 15 s**	10 min warm up Walking choice (9 min halves) *2 min rest at half time* 5 min cool down **Total time: 35 min**
4	7	10 min warm up Circuit training to music (5 reps of 45 s and 90 s rest) 5 min cool down **Total time: 26 min 15 s**	10 min warm up Walking choice (9 min halves) *2 min rest at half time* 5 min cool down **Total time: 35 min**
	8	10 min warm up Football (5 reps of 45 s and 90 s rest) 5 min cool down **Total time: 26 min 15 s**	10 min warm up Walking choice (9 min halves) *2 min rest at half time* 5 min cool down **Total time: 35 min**
5	9	10 min warm up Basketball (6 reps of 45 s and 90 s rest) 5 min cool down **Total time: 28 min 30 s**	10 min warm up Walking choice (10.5 min halves) *2 min rest at half time* 5 min cool down **Total time: 38 min**
	10	10 min warm up Choice/combination (6 reps of 45 s and 90 s rest) 5 min cool down **Total time: 28 min 30 s**	10 min warm up Walking choice (10.5 min halves) *2 min rest at half time* 5 min cool down **Total time: 38 min**
6	11	10 min warm up Boxing (6 reps of 45 s and 90 s rest) 5 min cool down **Total time: 28 min 30 s**	10 min warm up Walking choice (10.5 min halves) *2 min rest at half time* 5 min cool down **Total time: 38 min**
	12	10 min warm up Circuit training to music (6 reps of 45 s and 90 s rest) 5 min cool down **Total time: 28 min 30 s**	10 min warm up Walking choice (10.5 min halves) *2 min rest at half time* 5 min cool down **Total time: 38 min**
7	13	10 min warm up Football (8 reps of 45 s and 90 s rest) 5 min cool down **Total time: 33 min**	10 min warm up Walking choice (13.5 min halves) *2 min rest at half time* 5 min cool down **Total time: 44 min**
	14	10 min warm up Basketball (8 reps of 45 s and 90 s rest) 5 min cool down **Total time: 33 min**	10 min warm up Walking choice (13.5 min halves) *2 min rest at half time* 5 min cool down **Total time: 44 min**
8	15	10 min warm up Choice/combination (8 reps of 45 s and 90 s rest) 5 min cool down **Total time: 33 min**	10 min warm up Walking choice (13.5 min halves) *2 min rest at half time* 5 min cool down **Total time: 44 min**
	16	10 min warm up Boxing (8 reps of 45 s and 90 s rest) 5 min cool down **Total time: 33 min**	10 min warm up Walking choice (13.5 min halves) *2 min rest at half time* 5 min cool down **Total time: 44 min**
9	17	10 min warm up Circuit training to music (10 reps of 45 s and 90 s rest) 5 min cool down **Total time: 37 min 30 s**	10 min warm up Walking choice (16.5 min halves) *2 min rest at half time* 5 min cool down **Total time: 50 min**
	18	10 min warm up Football (10 reps of 45 s and 90 s rest) 5 min cool down **Total time: 37 min 30 s**	10 min warm up Walking choice (16.5 min halves) *2 min rest at half time* 5 min cool down **Total time: 50 min**
10	19	10 min warm up Basketball (10 reps of 45 s and 90 s rest) 5 min cool down **Total time: 37 min 30 s**	10 min warm up Walking choice (16.5 min halves) *2 min rest at half time* 5 min cool down **Total time: 50 min**
	20	10 min warm up Choice/combination (10 reps of 45 s and 90 s rest) 5 min cool down **Total time: 37 min 30 s**	10 min warm up Walking choice (16.5 min halves) *2 min rest at half time* 5 min cool down **Total time: 50 min**
11	21	10 min warm up Boxing (12 reps of 45 s and 90 s rest) 5 min cool down **Total time: 42 min**	10 min warm up Walking choice (2 × 10 min and 2 × 9 min quarters) *1 min rest between* 5 min cool down **Total time: 57 min**
	22	10 min warm up Circuit training to music (12 reps of 45 s and 90 s rest) 5 min cool down **Total time: 42 min**	10 min warm up Walking choice (2 × 10 min and 2 × 9 min quarters) *1 min rest between* 5 min cool down **Total time: 57 min**
12	23	10 min warm up Football (12 reps of 45 s and 90 s rest) 5 min cool down **Total time: 42 min**	10 min warm up Walking choice (2 × 10 min and 2 × 9 min quarters) *1 min rest between* 5 min cool down **Total time: 57 min**
	24	10 min warm up Basketball (12 reps of 45 s and 90 s rest) 5 min cool down **Total time: 42 min**	10 min warm up Walking choice (2 × 10 min and 2 × 9 min quarters) *1 min rest between* 5 min cool down **Total time: 57 min**

On arrival, participants get changed. They will also put the heart rate monitor on, and this will be demonstrated in an earlier session

*High-intensity interval training exercises*

Boxing

Reps can include any of the following:

• Ten jabs, followed by running to the end of the sports hall and back

• Ten hooks, followed by five squat thrusts

• Fast upper cuts

• Ten jabs, followed by five-star jumps

• Fast jabs

• Ten side steps, followed by running to the end of the sports hall and back

• Five combination punches (hook and jab), followed by running to the end of the sport hall and back

• Ten of favourite punch action, followed by ten tuck jumps

Circuit training to music

• Full star jumps

• Tuck jumps

• Stationary high knees runs

• Jumping with one hand in the air

• Hop on one leg

• Push ups

• Sit ups

• High leg kicks

• Fast side kicks

• Fast side to side twists

Football

• Ten toe touches, followed by running to a cone and back

• Running up to kick the ball ten times, followed by five burpees

• Sprinting around cones in the sports hall

• Kicking a football into a goal then running to end of the sports hall and back. Performing fast feet movements through cones then running to end of the sport hall and back

• Jumping up to head a football five times then running to the end of the sports hall and back

• Running around the sports hall following a square or diagonal course

Basketball

• Receiving and returning a chest pass, followed by running to a cone and back

• Running around in a square and receiving and returning a bounce pass on one corner of the square

• Bouncing a ball five times then running to the end of the hall and back

• Receiving a shoulder pass, followed by running to a cone and back

##### Low-intensity exercise arm

This is composed of low-intensity exercise of alternating training sessions [48] (e.g. walking football, walking netball). These activities elicit a heart rate between 40 and 50% maximal effort based on the activity compendium [49]. The sessions will follow the same warm up and cool down as the high intensity, but the overall exercise session will be longer (to energy match to high intensity). The first 2 weeks will start at 15 min of exercise with a 2-min break in the middle. This will increase by 3 min every 2 weeks for the first 6 weeks, and 6 min every 2 weeks for the second 6 weeks. The last 2 weeks will therefore consist of 38 min of exercise (including the break).

##### Energy matching

A pilot study was conducted to ensure that the low- and high-intensity arms will exert an equivalent amount of energy, using a standardised protocol [[name], [name], [name], [name], [name], [name], et al. Energy matching of a high intensity exercise protocol with a low intensity exercise protocol in adolescents. Under Review.]. This will ensure that any differences between groups will be down to intensity of exercise rather than the amount of energy expended. Following walking on a treadmill at a comfortable speed for 5 min, 24 participants (15 boys and 9 girls) completed the low-intensity exercise protocol for 10 min (walking football), rested until their heart rate had returned to baseline, and then completed the high-intensity interval exercise protocol (boxing), for 9 min. Nine minutes of the high-intensity exercise (e.g. four repetitions of 45 s of exercise and 90 s rest) was the equivalent of approximately 12 min of continuous low-intensity exercise.

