##### Social control arm

Social activities will include board and team games (e.g. giant Jenga), and group discussions, with the exact activities agreed upon by the group. The purpose of these control activities is to provide a comparative length of time (to the exercise groups) and social context, which does not involve exercise, to estimate any potential social benefits for depression of the two exercise conditions. The Healthy Living session will be the same as other trial arms to avoid introducing variables other than supervised exercise sessions into the study design. Young people in all three arms will be encouraged to engage in physical activity after the intervention ends to maintain their exercise levels.

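### The low-intensity schedule starts 3 min above the pilot's energy-match ratio and keeps that offset through week 10, and the weeks 11-12 durations contradict each other

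*Protocol article*

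**What the plan says.** The Energy matching section of the protocol article describes a pilot in 24 participants. Its result is that "Nine minutes of the high-intensity exercise (e.g. four repetitions of 45 s of exercise and 90 s rest" in each repetition) "was the equivalent of approximately 12 min of continuous low-intensity exercise". From this it concludes: "This will ensure that any differences between groups will be down to intensity of exercise rather than the amount of energy expended". The Methods paragraph of the abstract likewise describes the two exercise groups as matched on energy.

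The Low-intensity exercise arm section sets the durations: "The first 2 weeks will start at 15 min of exercise with a 2-min break in the middle". It continues: "This will increase by 3 min every 2 weeks for the first 6 weeks, and 6 min every 2 weeks for the second 6 weeks". It closes: "The last 2 weeks will therefore consist of 38 min of exercise (including the break").

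Table 1 gives every session. Weeks 1-2 have four high-intensity repetitions against two 7.5-min halves of walking games, with the 2-min rest listed separately. For weeks 11-12 the low-intensity entry is "Walking choice (2 × 10 min and 2 × 9 min quarters") with 1-min rests between quarters and a stated session total of 57 min.

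**The concern.** The schedule gives the 9-min high-intensity block a low-intensity partner of 15 min, while the pilot result given to justify the pairing is about 12 min. No reason is given for the extra 3 min. The final fortnight is also described in ways that cannot all be true.

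Two things are at stake. First, energy matching is a stated design property and the basis for reading a high-versus-low difference as an effect of intensity rather than energy. If the schedule does not follow the ratio, that reading is weaker than the text says, and a main trial could inherit the problem. Second, intervention logs record activity durations and are rated against an adherence checklist. As the article stands, sessions 21-24 have no single planned low-intensity duration to rate against.

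**Working it through.** **Inputs**
- Pilot ratio (Energy matching): 12/9 = 1.333 low-intensity minutes per high-intensity minute, rests included in the 9.
- High-intensity repetitions (Table 1): 4, 5, 6, 8, 10, 12 across the six fortnights, each 45 s + 90 s = 2.25 min.
- Low-intensity active minutes (Table 1): twice the stated half, or the sum of the quarters.
- Warm-up 10 min and cool-down 5 min in both arms.

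**Reproducing the plan's totals**
- High: 15 + repetitions × 2.25 = 24, 26.25, 28.5, 33, 37.5, 42. All agree with Table 1.
- Low, weeks 1-10: 15 + active + 2 = 32, 35, 38, 44, 50. All agree. The break is therefore counted outside the 15 min and does not explain the gap.
- Low, weeks 11-12: 10 + (2×10 + 2×9) + 3×1 + 5 = 56. Table 1 states 57.

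**Pilot-matched duration = high block × 12/9**

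| Weeks | High block (min) | Matched low (min) | Table 1 low (min) | Excess | Low:high ratio |
|---|---|---|---|---|---|
| 1-2 | 9 | 12 | 15 | 3 (25.0%) | 1.667 |
| 3-4 | 11.25 | 15 | 18 | 3 (20.0%) | 1.600 |
| 5-6 | 13.5 | 18 | 21 | 3 (16.7%) | 1.556 |
| 7-8 | 18 | 24 | 27 | 3 (12.5%) | 1.500 |
| 9-10 | 22.5 | 30 | 33 | 3 (10.0%) | 1.467 |
| 11-12 | 27 | 36 | 38 | 2 (5.6%) | 1.407 |

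**Source of the excess.** The high-intensity increments are 2.25 and 4.5 min, and the low-intensity increments are 3 and 6 min. 2.25 × 4/3 = 3 and 4.5 × 4/3 = 6, so the increments follow the ratio exactly. Through week 10 the schedule is 4/3 × high + 3 min. The falling percentages all come from one starting offset.

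**Weeks 11-12, by reading**
- Text progression: 15 + 3 + 3 + 6 + 6 + 6 = 39 active min (+8.3% against 36).
- Table 1 quarters: 38 active min (+5.6%).
- Text closing figure, 38 including a 2-min break: 36 active min (0%).
- Text closing figure with Table 1's three 1-min breaks: 35 active min (-2.8%).

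The text presents its closing figure as following from the progression, but it does not. If the initial 15 min excludes the break, the result is 39 active, or 41 with a 2-min break. If it includes the break, the result is 39 including it. The 57-min total would fit 39 active min with three 1-min rests (10+39+3+5) or 38 with four (10+38+4+5).

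**Whole course, four sessions per fortnight**
- High: 4 × (9+11.25+13.5+18+22.5+27) = 405 min.
- Matched low: 405 × 12/9 = 540 min.
- Planned low: 4 × (15+18+21+27+33+v) = 4 × (114+v), where v is the weeks 11-12 value.
- v = 35, 36, 38, 39 gives 596, 600, 608, 612 min, which is +10.4%, +11.1%, +12.6%, +13.3%.

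**The case against.** The strongest reply is that the pilot figure is approximate, comes from boxing against walking football, and is expressed in minutes. The article gives no energy values, and both arms share 15 min of warm-up and cool-down, so the proportional excess over a whole session is smaller. This stands as a limit on the size. It could cover the 5.6% in the last fortnight, but it hardly covers 25% in the first, where the same 9-min block is used. Scaling the ratio to longer blocks is an assumption, but the protocol's own increments make it too.

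It is also fair to say that no result of this trial will be confounded. The Statistical methods section rules out formal comparison of the groups, and the sample size is not powered for one. That limits the severity but does not remove the contradiction.

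A reader might infer more than the document supports:
- **That the excess holds in every week.** It does in weeks 1-10. In weeks 11-12, one reading of the text's closing figure meets the ratio exactly.
- **That the protocol claims the arms differ in nothing but intensity.** Its sentence contrasts intensity with energy expended only.
- **That unequal session length is itself an error.** The low-intensity section says openly that its sessions are longer in order to match energy, and a perfect 12:9 match would also leave unequal time. Comparing Table 1 totals alone (1024 against 765 min) overstates the contact difference, because all arms also have a 15-20 min Healthy Living portion at each of 24 sessions. With it the totals are 1384 against 1125 or 1504 against 1245 min, about 21% to 23% more.
- **That the social control cannot do what is promised.** The text asks only that it "provide a comparative length of time (to the exercise groups"). It does not promise identical length, and the exact duration may stand in the full protocol or manual.

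**Conclusion.** The concern holds. In weeks 1-10, where text and Table 1 agree with each other, the low-intensity main block exceeds the pilot-matched duration by a fixed 3 min, or 25% falling to 10%. In weeks 11-12 the documented values range from 35 to 39 active minutes against a matched 36, and Table 1's total is out by 1 min. The whole-course excess is about 10% to 13% of main-block minutes. Reading minutes as energy assumes a constant rate of expenditure in active play and a pilot ratio that transfers across durations and activities.

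The article's figures therefore do not support an unqualified statement that energy is matched. Which duration is right cannot be judged from the document. This should be fixed, but it does not threaten the feasibility outcomes. It matters for rating fidelity in sessions 21-24, for how any high-versus-low pattern is described, and for the main-trial design.

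**What to change.** - Reconcile the High-intensity exercise arm text, Table 1, the Low-intensity exercise arm text and the Energy matching section into one consistent schedule.
- Correct the weeks 11-12 entries (active minutes, breaks and session total) so that logs are rated against a single standard.
- Unless the reconciled schedule meets the pilot ratio, qualify the energy-matching statements in the abstract and the Energy matching section. State the planned low:high duration ratio per fortnight and the assumption that links minutes to energy.
- Summarise activity durations and heart rate by arm. The logs and monitors already record both, so no new data collection is needed.

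The cost is a correction to the text and Table 1, and to any delivery manual that repeats these figures. If the ratio is not met, the design claim becomes more modest but accurate.
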